## Abstract

**Background:**

Heart failure (HF) is a prevalent chronic disease and is associated with increases in mortality and morbidity. HF is a leading cause of hospitalizations and readmissions in the United States. A potentially promising area for preventing HF readmissions is continuous remote patient monitoring (CRPM).

**Objective:**

The primary aim of this study is to determine the feasibility and preliminary efficacy of a CRPM solution in patients with HF at NorthShore University HealthSystem.

**Methods:**

This study is a feasibility study and uses a wearable biosensor to continuously remotely monitor patients with HF for 30 days after discharge. Eligible patients admitted with an HF exacerbation at NorthShore University HealthSystem are being recruited, and the wearable biosensor is placed before discharge. The biosensor collects physiological ambulatory data, which are analyzed for signs of patient deterioration. Participants are also completing a daily survey through a dedicated study smartphone. If prespecified criteria from the physiological data and survey results are met, a notification is triggered, and a predetermined electronic health record–based pathway of telephonic management is completed. In phase 1, which has already been completed, 5 patients were enrolled and monitored for 30 days after discharge. The results of phase 1 were analyzed, and modifications to the program were made to optimize it. After analysis of the phase 1 results, 15 patients are being enrolled for phase 2, which is a calibration and testing period to enable further adjustments to be made. After phase 2, we will enroll 45 patients for phase 3. The combined results of phases 1, 2, and 3 will be analyzed to determine the feasibility of a CRPM program in patients with HF. Semistructured interviews are being conducted with key stakeholders, including patients, and these results will be analyzed using the affective adaptation of the technology acceptance model.

**Results:**

During phase 1, of the 5 patients, 2 (40%) were readmitted during the study period. The study completion rate for phase 1 was 80% (4/5), and the study attrition rate was 20% (1/5). There were 57 protocol deviations out of 150 patient days in phase 1 of the study. The results of phase 1 were analyzed, and the study protocol was adjusted to optimize it for phases 2 and 3. Phase 2 and phase 3 results will be available by the end of 2022.

**Conclusions:**

A CRPM program may offer a low-risk solution to improve care of patients with HF after hospital discharge and may help to decrease readmission of patients with HF to the hospital. This protocol may also lay the groundwork for the use of CRPM solutions in other groups of patients considered to be at high risk.

**International Registered Report Identifier (IRRID):**

DERR1-10.2196/36741

## Introduction

### Background

Heart failure (HF) is a growing global public health concern. Worldwide, the estimated prevalence of HF has increased to >37.7 million cases, and in the United States the estimated prevalence is 6.5 million cases [1,2]. HF is associated with increased mortality, morbidity, and loss of quality-adjusted life years [3]. HF also has a significant economic burden; it is estimated that the overall cost of HF in the United States was US $30.7 billion in 2012, and the total cost of HF hospitalizations in the United States was US $11 billion in 2014 [4,5]. HF is a leading cause of hospitalizations among adults in the United States, and Medicare patients with HF have the highest readmission rates, ranging from 17% to 28.2% [3,5].

HF readmissions have become an increasing focus of quality improvement, and many readmissions are viewed as preventable [4,5]. The Affordable Care Act initiated the Hospital Readmission Reduction Program, which imposes a financial penalty on hospitals with excess 30-day unplanned readmissions [6]. Although these measures have been somewhat effective, additional strategies are necessary to continue improvement in this metric [5]. A promising strategy for improving outcomes in HF, including readmissions, is the use of mobile health (mHealth) solutions.

### Related Works

The use of mobile apps is an area of mHealth strategies that have the potential to improve care for patients with HF. Patient-facing apps that focus on self-care and self-monitoring constitute one such area of interest. A meta-synthesis of mobile apps in cardiovascular disease found that mobile apps can help to improve modifiable risk factors for cardiovascular disease [7]. Schmaderer et al [8] developed a mobile app that enabled patients to record their daily weight and medication and provided patients with reminders and educational tips. The authors completed a randomized 3-arm trial that found that patients randomized to the mobile app group or the mobile app plus internet-based–visit group had a trend toward improvement in health-related quality of life [8]. Another study performed a randomized controlled trial on the impact of a mobile app that promoted self-management and daily self-monitoring and found a statistically significant improvement in the Minnesota Living with Heart Failure Questionnaire score at 6 weeks but not at 12 weeks [9]. Overall, interventions using mobile apps alone, without other support built in, have had limited success in improving outcomes in patients with HF [8,9]. However, mobile apps have the potential to improve health, given their prevalence and portability, as well as their ability to record data, connect people, monitor activity, and provide patient-centric health care solutions. Ultimately, there is a further need for systemic assessment of potential mobile apps [10]. In addition, it is possible that mobile apps built in as part of an mHealth solution, as opposed to being the sole intervention, might lead to a more significant improvement in health-related outcomes.

Another possible mHealth approach for improving HF outcomes is remote patient monitoring. These solutions include the use of wearable or implanted devices, mobile apps, or other electronic devices that transmit data to health care providers. Implantable devices have shown potential as one such option for remote patient monitoring. The CardioMEMS Heart Sensor Allows Monitoring of Pressures to Improve Outcomes in NYHA Functional Class III Heart Failure Patients trial evaluated the use of CardioMEMS, an implanted pulmonary artery pressure–monitoring device, and demonstrated a reduction in morbidity, mortality, and hospitalization rate in patients with HF [11]. Hindricks et al [12] performed a randomized controlled trial evaluating the use of implant-based multiparameter telemonitoring compared with usual care in patients with new implantable cardioverter defibrillators or cardiac resynchronization therapy defibrillators and found that the telemonitoring group had a lower mortality score. Overall, some invasive remote monitoring solutions have demonstrated improvements in mortality [11,12] and a decrease in health care costs [13], but they have the large disadvantage of the need for an implantable device, leaving a gap for less-invasive monitoring.

Several studies have investigated forms of noninvasive remote monitoring and their efficacy in improving outcomes in HF [14-30]. A study showing a benefit was the Telemonitoring in the Management of Heart Failure study, a randomized controlled trial that evaluated a remote monitoring device that measured body weight, blood pressure, and heart rate [17]. These parameters were obtained daily, and email alerts were sent to providers when predefined criteria for interventions were met. This intervention, compared with usual care, reduced mortality, number of days lost to hospitalization, and death [17]. Overall, results of noninvasive remote monitoring studies have been mixed, with some showing a benefit in reducing mortality [15,17,30], improvement in quality of life [14,19,24,25,28], and reduction in readmissions [15,18,23,24,28,30], whereas some showed an improvement in outcomes [9,23,24]. Nonetheless, most remote patient monitoring solutions have yet to take advantage of recent advances in biosensor devices and machine learning technologies and thus do not provide intelligent continuous patient monitoring. Furthermore, raw data are typically collected from patients and required to be funneled through already overtaxed clinical providers [31]. In addition, many of the noninvasive remote monitoring solutions for patients with HF have depended on data collected at discrete time points, as opposed to continuously collected data.

Data collected at discrete time points might limit insight into the patient’s health status and may not reflect their condition during activities of daily living. There is some evidence that continuous remote patient monitoring (CRPM) might improve outcomes for patients [32-35]. For example, Downey et al [32] compared continuous vital sign monitoring with discrete vital sign monitoring in patients hospitalized after surgery and found that the continuous remote monitoring of vital signs group had a shorter length of stay and had fewer readmissions than the discrete vital signs monitoring group. Several studies have demonstrated that noninvasive CRPM can be used to help predict readmissions in patients with HF [36-38]. For example, Anand et al [36] completed a nonrandomized, prospective trial of 314 patients with HF where they used vital signs collected from an external chest sensor to develop and validate an algorithm to predict decompensation in patients with HF. They found that the algorithm had 63% sensitivity and 92% specificity in the validation cohort [36].

The latest advance in CRPM is pairing it with advanced machine learning analytics. By using a patient’s continuous physiological data stream and applying machine learning analytics, it is possible to detect a change in health status that is unique to that patient and not measured against population norms. Promising data supporting this were presented in phase 1 of this study. We found that elevated respiratory rate for individual patients may be associated with readmission [39]. Furthermore, the Multisensor Non-invasive Remote Monitoring for Prediction of Heart Failure Exacerbation study found that with a sensitivity of 87.5% and specificity of 86%, the analytics were able to predict worsening HF (rehospitalization), with a median time between the initial notification of a variance in vital signs and readmission of 6.5 (IQR 4.2-13.7) days [38]. This suggests there may be time to intervene before decompensation and readmission.

### Study Development 

Because of the complex medical needs of patients with HF, it is thought that interventions to improve quality of life and health-related outcomes will need to be multipronged and complex [27,40]. Given this, small-scale feasibility pilot studies are useful to determine the feasibility of intricate interventions and allow for refinement of the intervention [41]. We developed an interest in the potential of mHealth solutions to improve outcomes in patients with HF and specifically wanted to study a CRPM system with machine analytics because we feel that this is an untapped area that has the potential to improve outcomes [32-36,38,39]. We therefore developed a cascading-alert continuous remote monitoring system. Because of the complexity of this intervention, we have opted to develop a multiphase pilot feasibility study, with plans for a separate efficacy trial at a later date after the system has been fine-tuned and determined to be feasible.

### Objectives

We hypothesize that a continuous noninvasive remote monitoring solution with machine learning analytics used in a population with HF will lead to an earlier and more accurate prediction of decompensation and help to prevent readmissions. Therefore, the objective of the Cascade study is to evaluate the feasibility and preliminary efficacy of a CRPM program at NorthShore University HealthSystem (NSUHS).

## Methods

### Study Design and Implementation

This is a prospective, mixed methods, nonrandomized, open-label feasibility study. Phase 1 (n=5) was the soft launch and has already been completed [39]. Phase 2 (n=15) is a calibration and testing period to evaluate, adjust, and optimize the alerting criteria, monitoring protocol, and workflows. Phase 3 (n=45) is the pilot period of the optimized study protocol. The study outcomes include feasibility and preliminary efficacy, as well as operational, process, and patient-related outcomes. Feasibility will be determined by evaluating provider and patient acceptability and satisfaction and by evaluating the study attrition and study completion rate. Provider and patient acceptability and satisfaction will be assessed through qualitative measures using the affective adaptation of the technology acceptance model (A-TAM) [42]. Preliminary efficacy will be determined by comparing the study group readmission rate with a retrospective cohort readmission rate.

The study will use the pinpointIQ (physIQ) solution to continuously remotely monitor patients with HF for 30 days after discharge. We will use rules-based and machine learning algorithms to analyze patients’ physiological data collected from the VitalPatch biosensor (VitalConnect) to identify patients potentially at risk of decompensation. A structured cascading escalation and management care pathway will be used to intervene on patients determined to be at risk for decompensation.

### Participants

Participants will be recruited at NSUHS, which is a 9-hospital integrated health system in Chicago and surrounding suburbs in Illinois, United States. The intervention will be implemented at Evanston Hospital, a 354-bed hospital located in the Chicago suburbs, which has a cardiac care unit and an advanced HF cardiology consult service.

### Recruitment

Eligible participants are recruited from patients hospitalized at NSUHS with an HF exacerbation. A daily enterprise data warehouse query is executed to identify patients hospitalized with an HF exacerbation who meet the eligibility determined by specific inclusion and exclusion criteria. Patients considered for participation have an HF diagnosis, have New York Heart Association functional class II to class IV symptoms, have received at least one dose of an intravenous (IV) diuretic during their hospitalization, have a plan for discharging with partnering home health services, speak English, and are in the top 50% of the patients stratified using NSUHS’s 30-day readmission risk–prediction model called the clinical analytics prediction engine [43]. Patients are not considered if they meet any of the exclusion criteria, which include having a CardioMEMS device; having an allergy to hydrocolloid gel adhesive; being pregnant; being on dialysis; or having a documented visual, cognitive, or physical impairment that would interfere with the ability to comply with the study procedures.

### Device and Notification Mechanisms

The study uses the pinpointIQ solution, which includes Food and Drug Administration–cleared analytics that can provide early indication of patient deterioration and is capable of generating clinician-defined–event notifications. This is a closed loop monitoring solution that comprises a medical-grade biosensor with remote data collection capabilities, a smartphone app that acts as a data hub and electronic patient-reported outcome (ePRO) interface, a cloud computing platform for applying personalized analytics to patient data, a clinician portal for viewing biosensor data and analytics results that generate notifications (Figure 1), and an application programming interface. An overview of the clinician portal interface is shown in Figure 2.

Study participants are provided a chest-worn VitalPatch biosensor to wear, which collects near–real-time continuous ambulatory vital signs, including heart rate, respiratory rate, heart rate variability, activity level, sleep-wake determination, position, and atrial fibrillation detection (includes single-lead telemetry) once discharged. The biosensor is a disposable noninvasive patch that lasts 7 days and is replaced multiple times by the patient in the postdischarge period to have active monitoring for 30 days in total. This biosensor is a vendor medical device and has been tested separately from this study.

A study-specific smartphone is provided to the participant. The vendor developed an Android smartphone app that serves as the gateway for real-time data acquisition through Bluetooth from the biosensor. It also provides an interface for ePRO questionnaires (Figure 3). The vendor used data from focus groups of patients with chronic illness in the age range of the typical user to inform the smartphone app design. The app runs on a dedicated locked smartphone that is configured only to run the app, which has been validated to reliably interface with, and collect data from, the biosensor. The app interacts with the biosensor in real time and uploads data directly to the vendor platform over a secure cellular network connection. The app also provides patients with indications for proper data collection and escalating notifications of potential data loss, including connectivity issues, low battery, low memory, and unanswered questionnaires (Figure 4). If a patient is out of range with the smartphone, the data are still collected and stored by the VitalPatch biosensor for 8 hours. When the patient comes back into range with the smartphone, the collected and stored physiological data start uploading to the cloud again. The study smartphone’s battery life is approximately 12 hours, and the patients are trained to charge the study smartphone daily.

The patient is given a separate study smartphone as opposed to using their own mobile phone for a few reasons. First, many older patients with HF do not own a smartphone; providing them with a study smartphone helps to include patients with HF who may otherwise be excluded from the study. Second, the study smartphone only contains the vendor’s app; if the patient ever loses the study smartphone, the vendor can remotely wipe the smartphone’s data to ensure that patient privacy is protected. The study smartphone is slim and easy to carry, and most patients do not find having 2 mobile phones inconvenient.

The physiological data are transmitted from the study smartphone to the cloud and analyzed by rules-based and machine learning algorithms to help identify risk of decompensation in patients with HF. The data transmission pathway is shown in Figure 5. Rules-based notifications include tachypnea, tachycardia, bradycardia, atrial fibrillation, and atrial fibrillation with rapid ventricular response. The multivariate change index (MCI), a machine learning–based notification, is also calculated from the physiological data [38]. The MCI is a nonspecific patient deterioration model that trains on the first 48 hours of a patient’s physiology and then measures the difference between expected and observed physiology and signals in the clinician portal when there is a significant difference in these measurements. The system specifically calculates an MCI in relation to heart rate and respiratory rate and evaluates for 3 different MCI notifications: MCI elevated heart rate, MCI depressed heart rate, and MCI elevated sleeping respiratory rate.

**Figure 1 figure1:**
[figure not shown]
Overview of the clinician portal showing the portal, possible clinician-defined events, and a notification. HR: heart rate; MCI: multivariate change index; RR: respiratory rate; RVR: rapid ventricular response.

**Figure 2 figure2:**
[figure not shown]
The clinician portal showing an alert and clinical events, where green dots represent events that have been seen already, and red dots represent new events.

**Figure 3 figure3:**
[figure not shown]
The daily symptom survey on the mobile app.

**Figure 4 figure4:**
[figure not shown]
Mobile app alerts.

**Figure 5 figure5:**
[figure not shown]
Data transmission pathway. ECG: electrocardiogram; HR: heart rate; RR: respiratory rate.

The patients also complete a daily symptom survey (Figure 3) on the study smartphone based on the criteria from the HF zone tool, which is transmitted to the clinician portal [44,45]. Physiological notifications and daily symptom survey data (ePROs) are visible to the home health nurse (HHN) on the clinician portal. If predetermined criteria from the physiological events and ePRO responses are met, a structured and predefined electronic health record (EHR)–based pathway of health care provider telephonic management is initiated. The HHN is the first human in the loop in the cascade. If HHN escalation criteria are met, advanced practice providers (APPs) and potentially HF specialists are notified based on the acuity, type of clinical event, and call roster.

### Workflow and Clinical Management

The workflow process map is shown in Figure 6. The HHN reviews the web-based platform daily for any clinical event–driven notifications. The daily ePRO, which includes the patient’s daily weight and whether they are having symptoms related to HF, is also reviewed [44,45]. If a patient reports any symptoms on a particular day, the patient survey will also ask whether the symptoms are getting better, worse, or the same the following day.

If there are any red zone symptoms reported, which include symptoms of chest pain, shortness of breath at rest, wheezing at rest, swelling of the hands or face, confusion, anxiety, or feeling as though they must sit up to breathe, the HHN will call the HF specialist or send the patient to the emergency department (ED).

If there are any new or worsening symptoms of shortness of breath, orthopnea, or lower extremity edema (yellow zone symptoms), the HHN will call the patient and complete the structured EHR documentation note. The HHN documentation note provides automated management recommendations based on the information filled out in the note. In the case of a note stemming from new or worsening yellow zone symptoms, recommendations include increasing the oral diuretic dose and considering an in-house evaluation. The note will be forwarded to the APP pool and the patient’s HF specialist. The APP in turn will schedule a telephone visit with the patient and determine whether the patient needs home IV diuresis. If so, they will provide a prescription for this, and home health services will start IV diuretics at home. The HF attending physician and the HHN will be alerted of this plan.

If the patient has a weight gain of ≥5 lb (≥2.3 kg) compared with their baseline weight, the HHN will call the patient and complete the structured documentation note. Potential automated recommendations to consider include escalating the oral diuretic dose. The HHN will route the note to both the HF APPs and attending physician. The APP will follow up with the patient and schedule a telephone visit with the patient. The APP will assess whether the patient needs home IV diuresis, and if so, they will prescribe it. This plan will be communicated to the HF attending physician and the HHN.

If there is an MCI event, the HHN will call the patient and complete the structured note. Management recommendations include sending a visiting HHN to draw a complete blood count, a complete metabolic panel, and an N-terminal pro–B-type natriuretic peptide, as well as possible oral diuretic dose escalation. The HHN will also call the APP and route their note to the APP and HF attending physician. The APP will schedule a telephone visit with the patient and follow up on any laboratory test results. On the basis of their telephone visit, the patient’s ePROs, and any laboratory test results obtained, the APP will form a clinical assessment regarding the patient. On the basis of this assessment the APP will determine whether any of the following is indicated: an escalation of the oral diuretic dose, an urgent in-person clinic visit, and whether the HF attending physician needs to be alerted.

If there is an atrial fibrillation with rapid ventricular response event, the HHN will call the patient and complete the structured EHR note, call the APP or HF specialist, and route the note to the APP pool and HF specialist, or send the patient to the emergency room. If the APP is alerted to an atrial fibrillation with rapid ventricular response event, they will review the vendor platform to assess the event and the patient’s vital signs obtained from the biosensor. They will also schedule an urgent telephone or video visit with the patient to further assess them. The APP will determine whether the patient needs to be sent to the ED or whether the patient can be safely managed at home. The APP will also discuss their assessment with the HF attending physician to ensure that they agree with the plan.

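### Orthopnea is a yellow zone symptom and having to sit up to breathe is a red zone symptom; no stated qualifier separates them, and the red trigger is worded two ways for an unchanged symptom

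*Protocol article*

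**What the plan says.** Everything at issue is in the protocol article, Methods, Workflow and Clinical Management.

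- **Red zone list.** It starts with "chest pain, shortness of breath at rest, wheezing at rest" and its last item is "feeling as though they must sit up to breathe".
- **Red trigger and action.** The condition is "If there are any red zone symptoms reported", and then "the HHN will call the HF specialist or send the patient to the emergency department (ED").
- **Yellow zone list and trigger.** "If there are any new or worsening symptoms of shortness of breath, orthopnea, or lower extremity edema (yellow zone symptoms").
- **Yellow action.** "the HHN will call the patient and complete the structured EHR documentation note". The note then goes to the advanced practice provider (APP) pool and to the patient's HF specialist, and the APP arranges a telephone visit.
- **Follow-up question.** A patient who reports a symptom is asked the next day whether it is better, worse or the same, so an unchanged symptom is a status the survey records.
- **More than one alert.** Later in the same section, the more severe alert determines the pathway, with red ranked above yellow. This ranking describes the red tier as symptoms that are new or worsening.

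The article defines neither orthopnea nor the sit-up item. The survey screen (Figure 3) and the workflow map (Figure 6) are not shown.

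**The concern.** In ordinary clinical usage orthopnea is breathlessness on lying flat that is eased by sitting up. The red item reads like a lay description of the same thing. The text therefore places overlapping descriptions of one symptom in two tiers that have different triggers and different first actions, and it does not say how to tell them apart.

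The article shows elsewhere how it grades a symptom: shortness of breath is yellow in general and red when it occurs at rest. If two grades of orthopnea are intended, the distinguishing term is missing from the paragraphs that state the rule.

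The first consequence is for patient safety, because the urgency of the first response may depend on wording. There is also an indirect consequence for the evaluation. The cascade is the intervention under test, and the Discussion presents standardized initial nurse decisions as one of its merits. Table 2 counts protocol deviations against patient days, and a departure from the triage rule is hard to judge where the rule leaves the tier open.

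**Working it through.** No formula or stated figure is involved, so the check sets the rules side by side and runs through the cases.

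**Inputs** (all from Workflow and Clinical Management): the red list, trigger and action; the yellow list, trigger and action; the rule for more than one alert and its severity order. One assumption comes from outside the article: orthopnea carries its ordinary meaning, so that one breathing difficulty could be recorded under either label.

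**Step 1: is there a qualifier?**

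| Symptom | Yellow entry | Red entry | What separates them |
|---|---|---|---|
| Shortness of breath | unqualified | at rest | at rest |
| Breathlessness relieved by sitting up | orthopnea | must sit up to breathe | nothing stated |

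**Step 2: which pathway follows?** Three ways of recording the state times two statuses give six cases.

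| Recorded as | New or worsening | Unchanged |
|---|---|---|
| Both items | Both alerts fire; the severity order selects red | Red by the red zone paragraph; unclear by the severity ranking; no yellow alert |
| Sit-up item only | Red | Red by the red zone paragraph; unclear by the severity ranking |
| Orthopnea only | Yellow | No yellow alert |

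**Step 3: reading the table.**

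- With both items recorded and the symptom new or worsening, there is one answer, red, and the yellow entry for orthopnea has no effect.
- With one item recorded and the symptom new or worsening, the label decides between red and yellow.
- With the symptom unchanged, the label decides between a red alert and no yellow alert. The red side is itself uncertain, because the red zone paragraph takes any report while the severity ranking mentions only new or worsening symptoms.

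**Step 4: extent.** One of the three yellow symptoms is involved (shortness of breath, orthopnea, lower extremity edema). One of the seven red symptoms is involved (chest pain, shortness of breath at rest, wheezing at rest, swelling of hands or face, confusion, anxiety, having to sit up to breathe). The article gives no alert frequencies by symptom, so the proportion of alerts affected cannot be calculated.

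**The case against.** The strongest reply is that the severity order already settles the matter: a patient who meets both entries follows the red pathway. A reader might infer that one patient state leads to two pathways at once, and the article does not support that. The reply succeeds when both items are recorded. It does not help when only one is.

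A second reply is that sameness is an inference. Neither term is defined, the survey is built on an existing HF zone tool, and orthopnea may be shorthand for a graded survey item. Figures 3 and 6 might show this. That possibility stands and limits confidence. It does not change the fact that the written rule, as published, lacks the qualifier it uses for shortness of breath.

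A third reply is that the gap between the tiers is smaller than it looks. A reader might infer that unchanged orthopnea is either no alert or an emergency-department alert. That is too strong: red means a call to the HF specialist or a transfer to the emergency department, and the severity ranking leaves an unchanged red symptom unclear. For new or worsening symptoms, yellow also reaches the specialist through the forwarded note. What remains is a difference in the first step and its urgency.

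It can also be said that the severity ranking only orders alerts and does not define triggers, so its wording may be loose shorthand. That is possible, but the two wordings still need to agree.

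Finally, clinical judgment is left to the provider. That statement concerns care after the nurse has escalated, whereas the zone applies before that.

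**Conclusion.** The point holds as an undefined boundary in the triage rule. Overlapping descriptions sit in two tiers without a qualifier, so the pathway depends on the label when only one is recorded. The difference is sharpest for an unchanged symptom, where the article's two wordings of the red trigger also disagree. The conclusion rests on the ordinary meaning of orthopnea and on the written text alone; the figures that are not shown could narrow or remove the overlap.

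The size is one item in each tier and an unknown share of alerts. No primary end point definition, sample size or planned comparison is affected. It is worth correcting because the possible gain is in patient safety and consistent delivery of the intervention, and the change is small.

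Three stronger readings that a reader might infer are not supported:

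- **That the structured note sends the same report to either tier.** In the yellow pathway the note is completed after the alert, the red pathway mentions no note, and nothing says the note assigns the zone.
- **That notification counts cannot be compared across nurses or phases.** Nothing says nurses choose between the labels, and phase 1 used a different symptom survey that was later replaced, so that break exists regardless.
- **That analyses of red against yellow alerts are damaged.** None is planned. Table 2 lists the share of notifications answered within 24 hours without a split by zone, and the pattern mining relates monitoring data to clinical events.

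**What to change.** Reconcile the red and yellow symptom lists in Workflow and Clinical Management, and align the red trigger in the red zone paragraph with the severity ranking. Each daily survey item should map to exactly one zone with one trigger condition, including what happens when the symptom is unchanged. If two grades of the symptom are intended, write out the qualifier, as is done for shortness of breath. Use the same mapping in the survey, the structured note and Figure 6. Which tier and which trigger apply is for the clinical team to decide.

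The cost is protocol wording and a short mapping table, with no new data. Phase 2 is described as the period for adjusting alerting criteria, so the change fits there. If the survey wording in Figure 3 already separates the two items, only the text needs to be brought into line with it.
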